## Abstract

**Background:**

Type 2 diabetes mellitus (T2DM) is a common metabolic disease with significant health, social, and economic consequences. Traditional Chinese medicine (TCM) could effectively regulate blood sugar and influence gut microbiota in T2DM patients. Preliminary studies showed that the Coptis root and ginseng (RG) formula could relieve insulin resistance and prevent the progression of diabetes in mice.

**Objectives:**

The purpose of this study is to explore the efficacy and safety of RG formula in the treatment of adult patients with T2DM, as well as observing its effects on gut microbiota.

**Methods and analysis:**

This trial is a randomized, double-blind, placebo-controlled study. A total of 60 participants will be randomized in a 1:1 ratio into an experiment group (RG formula) and a control group (placebo). Patients in both groups will be given diabetes education and basic blood glucose control. Glucose-lowering drugs with significant influence on gut microbiota will be avoided. This trial will last 25 weeks including 1-week run-in, 12-week intervention, and 12-week follow-up visit. The primary outcome is the change in the HbA1c. The secondary outcomes comprise the change in the fasting blood glucose (FBG), postprandial blood glucose (PBG), fasting insulin (FIL), fasting C-peptide(C-P), insulin resistance index (IRI), inflammatory factors, and species abundance of gut microbiota between the two groups. Safety of medication will also be evaluated. The correlation analysis will be explored between the glycemic indicators, inflammatory factors, and abundance of gut microbiota.

**Discussion:**

This study will provide the clinical evidence for the efficacy of RG formula in regulating blood sugar and influencing gut microbiota, which will be beneficial to form the integrated therapeutic regimen in T2DM with TCM.

**Trial registration:**

“Clinical Study on the Intervention of Coptis Root and Ginseng,” Chinese Clinical Trials Registry ChiCTR 2100042126. Registered on 14 January 2021

**Supplementary Information:**

The online version contains supplementary material available at 10.1186/s13063-022-06229-5.

## Background

Diabetes mellitus (DM), which is caused by absolute or relative insulin deficiency and reduced sensitivity of target cells to insulin [1], is a common metabolic disease with significant health, social, and economic consequences. Around 1 in 11 adults worldwide now have been diagnosed with DM, 90% of whom are type 2 diabetes mellitus (T2DM) [2]. According to the 2017 survey by China’s National Center for Disease Control and Endocrinology Branch of the Chinese Medical Association, the prevalence rate of T2DM in China was 12.8%. China has become the country with the largest number of diabetes patients worldwide [3]. Patients with T2DM have a twofold to tenfold higher risk of cardiovascular disease-related death than age-matched normoglycemic individuals and are at substantially higher risk of all-cause mortality, cardiovascular complications (such as coronary heart disease, heart failure, stroke, and peripheral arterial disease), and microvascular complications (including retinopathy, neuropathy, and nephropathy), which seriously threatens their quality of life and brings heavy burden to the society [4].

Gut microbiota is closely related to diabetes. A Chinese research team has clarified the differences in gut microbiota between diabetic patients and healthy people at the molecular level by using metagenomic association analysis [5]. A series of studies in Gordon’s lab showed that the gut microbiota in patients with T2DM was characterized by a decrease in the abundance of butyrate-producing bacteria, such as *Bacteroidetes*, and an increase in various opportunistic pathogens, such as *Firmicutes* [6, 7]. Larsen found that in diabetic patients *Firmicutes* including *Clostridium* significantly reduced, while *Proteobacteria* which was positively correlated with blood glucose concentration significantly increased [8]. From normal glucose tolerance to pre-diabetes and then to the occurrence of T2DM, the relative abundance of *Streptococcus* continued to decline, while the relative abundance of *Verrucosa* and *Proteobacteria* showed an opposite trend, indicating that dysregulation of gut microbiota was associated with the progression of T2DM [9]. Some scholars proposed that gut microbiota influenced the occurrence and development of T2DM mainly through mechanisms such as the effect of intestinal energy acquisition [10–12], regulation of fat storage, influence of adipokines [13–15], and regulation of inflammation induced by metabolic endotoxemia [16].

Traditional Chinese medicine (TCM) could treat T2DM by regulating the disturbance of gut microbiota. A meta-analysis on TCM improvement of gut microbiota in the treatment of T2DM showed that TCM generally reduced fasting blood glucose and postprandial blood glucose and improved insulin resistance by means of enriching the relative abundance of bacteria in the genera *Bacteroides* [17]. To a specific degree, different TCM interventions could play a complex role in the various bacteria. On the one hand, the traditional formula such as GGQL and AMC formula has been proved to remodel the structure of gut microbiota. The GGQL formula, which consists of Radix Puerariae, *Scutellaria baicalensis*, Coptis root, and Radix liquiritiae, could enrich the abundance of intestinal beneficial bacteria like *Clostridium leptum* and inhibit the growth of intestinal pathogenic bacteria like *Fusobacterium*, thus improving the permeability of intestinal mucosa and treating T2DM [18]. The AMC formula, whose components are Rhizoma Anemarrhenae, Momordica charantia, Coptis root, Aloe vera, and red yeast rice, may ameliorate T2DM with hyperlipidemia by enriching beneficial bacteria, such as *Blautia* and *Faecalibacterium* spp. [19]. On the other hand, TCM extracts like ginseng polysaccharides and berberine also had a good effect in modulating gut microbiota structure as a potential mechanism for the improvement of T2DM. Studies showed that berberine could selectively inhibit the growth of *Blautia*, *Allobaculum* [20], *Ruminococcus gnavus*, *Ruminococcus schinkii*, *Lactobacillus acidophilus*, *Lactobacillus murinus*, and *Lactococcus lactis* [21], which may explain its effect on improving adipose infiltration and insulin resistance in high-fat diet-fed rats. Ginseng polysaccharides were confirmed to reverse the dysbiosis of intestinal flora in diabetic rats at the phyla level to approach the homeostasis mainly by increasing the relative abundance of *Firmicutes* and decreasing that of *Bacteroidetes* [22].

Previous studies found that the formula of Coptis root and ginseng (RG) could reduce postprandial blood glucose by inhibiting intestinal α-glucosidase in T2DM patients [23]. Our team also demonstrated that the RG formula could alleviate insulin resistance in diabetic rats through inhibiting the expressions of pro-inflammatory factors and pro-apoptotic factors in pancreatic islets, up-regulating adiponectin receptors, and reducing the level of serum-free fatty acids [24, 25]. Whether long-term intervention of RG formula will remodel the structure of gut microbiota, reduce inflammation, and improve insulin resistance is worthy to be explored. Based on the viewpoint of gut microbiota, this study aims to (1) assess the clinical efficacy of RG formula in adults with T2DM, (2) characterize the influence of RG formula on levels of inflammatory cytokines and structural changes of gut microbiota, and (3) analyze the relationship between changes in gut microbiota, inflammatory cytokines, and clinical assessments, in order to demonstrate the underlying mechanism of TCM treatment in T2DM patients.

## Methods

### Study design

This protocol is designed as a randomized and placebo-controlled trial. Participants and investigators are blinded. A total of 60 subjects will be recruited at the Section II of Endocrinology & Nephropathy department of Dongzhimen Hospital affiliated to Beijing University of Chinese Medicine. They will be randomized in a 1:1 ratio to an experiment group (RG formula) and a control group (placebo). Patients in both groups are given basic blood glucose control. Only the use of insulin and insulin secretion promoters (such as thiazolidinedione and sulfonylurea) can be allowed as basic control in both groups, as current research has shown no significant influence on gut microbiota in neither drugs. The trial flow diagram is illustrated in Fig. 1. The SPIRIT Checklist is shown in Supplemental file 1 [26].

**Fig. 1 Fig1:**
[figure not shown]
The trial flow diagram

### Participants

#### Diagnostic criteria

The diagnostic criteria for this trial will be set based on the American Diabetes Association (ADA) guidelines in 2018 [27]: (1) Patients with typical diabetes symptoms and random blood glucose ≥11.1 mmol/L or random venous plasma glucose ≥11.1 mmol/L. Typical symptoms of diabetes include polydipsia, polyphagia, polyuria, dysphoria, and weight loss without other triggers; (2) FBG or venous plasma glucose ≥ 7.0 mmol/L, which is defined as no calorie intake for at least 8 h; (3) PBG after OGTT test ≥ 11.1 mmol/L; and (4) HbA1c ≥ 6.5%.

#### Inclusion criteria

Patients who meet the following criteria will be considered for enrollment: (1) age 18–65; (2) meet the diabetes diagnostic criteria of ADA; (3) FBG is stable at less than 7 mmol/L and PBG is stable at less than 10 mmol/L; and (4) informed and consented. The process of obtaining informed consent shall comply with Good Clinical Practice (GCP).

#### Exclusion criteria

Patients are excluded if any of the exclusion criteria are met: (1) new-onset of T2DM, who should take metformin orally as recommended by guidelines ; (2) patients with cardiac insufficiency (B-type natriuretic peptide is greater than the upper limit of normal) or with impaired liver function (alanine transaminase and aspartate aminotransferase are twice greater than the upper limit of normal) or impaired kidney function (serum creatinine is greater than the upper limit of normal) or mental illness; (3) patients who had diabetic ketosis, diabetic ketoacidosis, or severe infection within 1 month before recruitment; (4) patients who are allergic to Coptis root or ginseng; (5) patients who receive antibiotics and weight-reducing medicine or have participated in other clinical trials within 1 month before recruitment; (6) patients who have inflammatory bowel diseases like ulcerative colitis and Crohn’s disease; and (7) pregnant or lactating women.

#### Withdrawal criteria

Participants who meet any of the following conditions will be removed from the study: (1) those who have poor medication adherence during the run-in period; (2) who can hardly not tolerate the side effect of experimental medicine; (3) who have severe cardiovascular and cerebrovascular complications or infections during the study observation; (4) who are unable to participate in the following visit in time within a week and refuse to be contacted after more than three telephone communication by researchers; and (5) who have intermittent use of probiotics and other Chinese patent medicine during the study.

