#### Allocation concealment mechanism

The random number sequence generated by the system will correspond to the number of the sixty subjects one by one. These numbers are then arranged from small to large (in those with the same random number, the one which is picked out first will be arranged in the front). One to 30 will be designated as the experimental group while 31–60 are the control group. The documents of the random process and randomization list will be enclosed in an opaque envelope. Participants, researchers, and coordinators together with statisticians are not aware of the allocation of the patient and remain unaware until trial completion. The randomization of allocation and concealment of allocation are completed by two researchers who do not communicate with each other.

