### Sample size

Sixty participants (*n* = 60) will be recruited after the run-in period and allocated to the RG group (*n* = 30) and the placebo group (*n* = 30). The sample size was calculated considering the expected change of glycosylated hemoglobin (HbA1c) (primary outcome) of the participants by software PASS15.0. Previous studies have reported that formula including Coptis root and ginseng had statistically and clinically significant reduction of absolute HbA1c by about 0.72% [34, 35] and mean change in HbA1c by about 0.70% [36]. The sample size was calculated to have 80% power to detect a moderate 0.65-SD difference in HbA1c, with an alpha/*α* value of 0.05. Additional participants will be recruited until the required number is achieved (*n* = 30) per group to account for the estimated drop-out rate of 15%. Therefore, we take the sample size as 30 in both groups.

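### Participants are removed from the study, not only from study drug, for events after randomisation, so the week-12 HbA1c can be lost unevenly by arm; the top-up sentence also needs reconciling with a closed list of 60

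*Protocol article*

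**What the plan says.** The Withdrawal criteria list five conditions under the lead-in "Participants who meet any of the following conditions will be removed from the study". Condition 1 concerns adherence in the run-in, and condition 4 concerns people who miss a visit and refuse further contact. The other three are those "who can hardly not tolerate the side effect of experimental medicine", those "who have severe cardiovascular and cerebrovascular complications or infections during the study observation" and those "who have intermittent use of probiotics and other Chinese patent medicine during the study".

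Table 1 (Study setting) places random grouping in the screening/baseline column. It schedules HbA1c at baseline, medication week 12 and the follow-up visits, and not at medication weeks 4 or 8. The primary outcome is the between-group comparison of HbA1c change after 12 weeks.

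The Sample size section claims "80% power to detect a moderate 0.65-SD difference in HbA1c" and handles losses with this sentence: "Additional participants will be recruited until the required number is achieved", at 30 "per group to account for the estimated drop-out rate of 15" per cent. It concludes with 30 in both groups. Study setting fixes enrolment at 60. The Allocation concealment mechanism matches the random sequence one by one to sixty subjects and splits it by rank: "One to 30 will be designated as the experimental group", with 31 to 60 as control. Under Implementation, the group manager keeps the list throughout.

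**The concern.** Stopping study drug and leaving the study are different events, and the Withdrawal criteria treat them as one. The Safety assessment section does speak separately of drug withdrawal, so the distinction is available to the authors.

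Randomisation protects the comparison only while outcomes are obtained from the people who were randomised. Conditions 2, 3 and 5 act after allocation. Condition 2 is tied to the product itself: the Safety assessment section names diarrhoea, abdominal pain and constipation as possible effects and attributes gastrointestinal irritation to Coptis root, whereas the placebo is dextrin and condiment. If people removed for such reasons also have a different HbA1c course, and more of them come from one arm, those who remain are no longer comparable groups. Later adverse-event visits are lost for the same people, although safety is a stated objective.

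The Sample size sentence adds a second problem. Read as replacement, it asks for participants whom the 60-number list cannot allocate, in numbers that depend on which arm the leavers came from.

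**Working it through.** **1. Is the primary value lost?** HbA1c falls at week 0, week 12 and follow-up weeks 4, 8 and 12. A participant removed before week 12 has no post-baseline HbA1c. An analysis plan could then only impute the value. A participant removed after week 12 already has it.

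**2. The plan's own sample size.** Inputs from the Sample size section: 0.65 SD, 80% power, alpha 0.05, 15% dropout. The Statistical analysis section makes all tests two-sided.
- Two-sided: n = 2(1.960 + 0.842)² / 0.65² = 37.2, so 38 per group (39 by the exact t-test). After loss, 38/0.85 = 44.7, so 45 (46 from the t-test figure).
- One-sided: n = 2(1.645 + 0.842)² / 0.65² = 29.3, so 30 per group (29.97 by the t-test). After loss, 30/0.85 = 35.3, so 36.

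The stated 30 is not reproduced from two-sided inputs. It matches only the one-sided figure before any allowance for dropout. That mismatch is a separate defect; here it matters only for how the top-up sentence is read.

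**3. The top-up sentence under its two readings.**
- *Replacement until 30 per group have data:* 60/0.85 = 70.6, so 71 to 72 randomised (36 per group gives 72). That is 11 to 12 more than the list holds, and no rule covers a 61st participant.
- *Ordinary inflation, 60 randomised in all:* 30 × 0.85 = 25.5 per group with data. Two-sided normal power is Φ(0.65·√(25.5/2) − 1.96) = Φ(0.361) = 64% (62% by the t-test). With all 30, it is Φ(0.65·√(30/2) − 1.96) = Φ(0.557) = 71% (70% by the t-test).

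**4. Possible size of the bias.** The documents give neither removal rates by arm nor any link between removal and HbA1c, so both are assumptions. Take a standard normal outcome, and remove a proportion p according to a propensity correlated r with it. The mean of those remaining shifts by r·φ(z_p)/(1 − p), where z_p cuts off the tail p. The factor φ(z_p)/(1 − p) is 0.109 at p = 5%, 0.195 at 10%, 0.350 at 20% and 0.424 at 25%. With no true effect, the spurious difference is:

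| Removal (one arm v other) | r = 0.3 | r = 0.5 |
|---|---|---|
| 20% v 10% | 0.3 × 0.155 = 0.046 SD | 0.5 × 0.155 = 0.077 SD |
| 25% v 5% | 0.3 × 0.315 = 0.095 SD | 0.5 × 0.315 = 0.158 SD |
| Equal in both arms, same r | 0 | 0 |

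With 30 analysed per group, the standard error is √(2/30) = 0.258 SD. The 0.077 shift is 0.30 of that and the 0.158 shift is 0.61. The largest entry is 0.158/0.65 = 24% of the target difference. If those removed were doing worse and came mostly from the RG arm, the shift would favour RG; the reverse pattern would reverse the sign.

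**The case against.** **The size is modest and assumed.** This stands. The 20% versus 10% case averages the protocol's own 15% and gives under a third of a standard error. The 25% versus 5% case has no basis in the documents.

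**A reader might infer that the plan specifies a completers-only comparison.** It does not. No analysis set is named, and a statistical analysis plan may define one. Conditions 3 and 5 also run through the 12-week follow-up, when the primary value already exists. What stands is narrower: removal before week 12 means the value is not collected, and naming an analysis set does not bring it back.

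**A reader might infer that removals will fall on the RG arm.** The Safety assessment section speaks only of a possibility of gastrointestinal effects and describes managing them with the medicine continued. Uneven removal is plausible, not shown.

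**A reader might take replacement as settled.** The Sample size section never says that dropouts are replaced, and a fixed total of 60 fits ordinary inflation. The match to an uninflated one-sided 30 hints at a completer target, but two-sided testing contradicts that derivation, so neither reading reproduces the stated inputs. The text is ambiguous.

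**A reader might infer that refilling a group must break the blind or make allocation predictable.** Those said to be unaware are participants, researchers, coordinators and statisticians. The group manager holds the list and could act alone, and recruitment and follow-up staff are barred from allocation information. It remains true that someone would have to use the leavers' allocations, and that no procedure is described.

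**Conclusion.** The point holds in two parts of unequal strength.

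The firm part is the removal rule. It takes participants out of the study for post-randomisation events that may differ by arm, and the visit schedule means that removal before week 12 forfeits the primary outcome. Any bias is of unknown size: about 0.05 to 0.08 SD for 20% versus 10% removal and up to about 0.16 SD for 25% versus 5%, both resting wholly on assumed correlations of 0.3 to 0.5, and nil if removal is equal and equally related to outcome in both arms. The case for change rests on avoidable loss of the primary outcome, not on a demonstrated large bias.

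The second part is a need to reconcile. The Sample size sentence can be read as replacement. On that reading it conflicts with the total of 60 and with a list that has no number for a 61st participant. The documents do not support going further and saying that replacements will occur, that the blind will fail, or that the analysis is restricted to completers.

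**What to change.** **Withdrawal criteria.** Separate stopping study drug from leaving the study. Ask participants who meet conditions 2, 3 or 5 to stay for the week-12 HbA1c and the safety visits, and analyse them in their randomised arm, with a per-protocol analysis as sensitivity. Which events stop study drug is left to the investigators. Condition 1 lies in the run-in and is not part of this point; condition 4 concerns people who refuse contact, whom this change cannot retain.

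**Sample size, with Study setting and Allocation concealment mechanism.** State that 60 are randomised, without group-specific replacement. Restate two-sided power at 0.65 SD as about 70–71% with all 30 per group and about 62–64% if 15% are lost. These are unadjusted figures. The planned covariance analysis could raise them, but the documents give no baseline correlation. As an assumption, r = 0.5 would need 28 per group (33 after loss) and r = 0.6 would need 24 (29 after loss).

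**Cost.** The change needs an amendment by the route the protocol describes, a few extra visits, some dilution of the estimate from non-adherers, and a less favourable stated power. Removing the top-up sentence also removes the only stated provision for dropout, which makes retention matter more. The Trial status section reports 44 already recruited; the change cannot recover week-12 values for any of them already removed.

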### Study setting

The treatment will be conducted at Dongzhimen Hospital affiliated to Beijing University of Chinese Medicine. The study will enroll 60 individuals in total, with 30 individuals in each group. Patients who are included in the study are required to sign an informed consent form. The researchers will spend 10–15 min informing the patients of the benefits and possible risks according to the statement in the informed consent. The informed consent form is provided in Supplemental file 2. An overview of specific measurements and time points of data collection is provided in Table 1.

**Table 1 Tab1:** Measurement items and point of data capture

Visit project		Screening period/baseline	Visit 1	Visit 2	Visit 3	Visit 4-6
Visiting time		–7 to 0 days	Medication week 4	Medication week 8	Medication week 12	Follow-up weeks 4, 8, and 12
Collect basic medical history						
Sign informed consent		√				
Fill in general information		√				
Medical history and treatment history		√				
Determine inclusion and exclusion criteria		√				
Physical examination		√	√	√	√	√
Comorbidity and medication records		√	√	√	√	√
Effectiveness observation						
Glycosylated hemoglobin		√			√	√
Fasting blood glucose		√			√	√
Postprandial blood glucose		√			√	√
Fasting insulin		√			√	
Fasting C-peptide		√			√	
Inflammatory factors		√			√	
Other work						
Random grouping		√				
Fecal specimen		√			√	√
Liver and kidney function		√			√	√
Adverse event		√	√	√	√	√

